#### Primary outcome measures

##### Endothelial function

FMD will be measured with the technique introduced by Ramírez-Vélez et al. [36] in the Colombian population using the guidelines reported by Corretti et al. [37]. The diameter of the brachial artery will be assessed using a high-resolution ultrasound device (Acuson Sequoia C512, Acuson Siemens, Mountain View, CA, USA), equipped with a 7.5–10-MHz linear array transducer and an integrated electrocardiography package. The ultrasound procedures will be performed with the subject resting quietly in a supine position for at least 10 min. Measurements will be performed in the morning (06.00–08.00 hours) due to diurnal variation in a climate-controlled room (18–20 °C) with the lights dimmed. All measurements will be taken at the end of diastole as observed by electrocardiogram. First, the diameter of the right brachial artery will be searched in a cross-sectional view and then scanned over a longitudinal section 5 to 10 cm proximal to the right elbow. The diameter of the brachial artery will be measured from the anterior to the posterior intima-lumen interface at a fixed distance, calculating the mean diameter from four cardiac cycles. After this, a pneumatic tourniquet placed around the right forearm will be rapidly inflated to at least 50 mmHg above the systolic blood pressure for 5 min. A sudden release of the cuff will induce an increase in blood flow in the brachial artery located proximal to the tourniquet. During reactive hyperaemia, shear stress will increase, causing endothelium-dependent vasodilatation, mainly due to endothelial release of nitric oxide [38, 39]. This secondary dilatation enhances and prolongs the reactive hyperaemic phase. FMD of the brachial artery will be measured 45–60 s after cuff release. The change in diameter caused by the increased flow will be calculated as the percentage change relative to the baseline measurement (FMD%). The intra-session coefficients of variation will be up to 1 % for baseline diameter. Reliability, estimated by intra-class correlation coefficients (ICC) based on four baseline measurements (*n* = 8 subjects), showed an ICC of 0.91 for the baseline diameter and 0.83 for FMD (*own date*). Images will be recorded on a DVD player for subsequent measurements by one observer blinded to the study.

#### Secondary outcomes

##### Heart rate variability

Measurement of HR variability will be performed according to current recommendations by the European Society of Cardiology using an evaluated share-ware (Kubios, vers. 2.0; http://kubios.uef.fi/) [40]. The variations in interbeat intervals in the time domain will be quantified by the mean values and standard deviations of normal interbeat intervals in the supine position.

##### Aortic pulse wave velocity (PWV) and augmentation index (AIx)

Both PWV and AIx will be measured with the oscillometric method using the occlusion technique. Patient data and the measured distance between the jugulum and the symphysis will be registered in the arteriography-programmed computer (TensioMed Software v.1.9.9.2; TensioMed, Budapest, Hungary). A tape measure will be used for measuring the distance between the jugulum and the symphysis, namely the aortic distance. The cuff will be placed on the patient’s upper arm and connected to the device. Pressure variations in the cuff will influence a pressure receptor and the signal, and will then be transferred via an infrared port to the computer. The algorithm measuring blood pressure in the arteriography device has been validated [41]. PWV will be calculated as the jugulum and the symphysis distance (m) divided by return time (return time/2) (s). For PWV, two recordings with the lowest standard deviation will be chosen. The standard deviation will be calculated from every heartbeat during a period of 8 s. Both aortic AIx (AIxao) and brachial AIx (AIxbr) will be calculated as:$$ 100\times \left(\mathrm{early}\ \mathrm{systolic}\ \mathrm{pressure}\ \mathrm{peak}-\mathrm{late}\ \mathrm{systolic}\ \mathrm{peak}\right)/\left.\mathrm{pulse}\ \mathrm{pressure}\right). $$

The return time is the difference (in ms) between the first (early systolic pressure peak) and reflected systolic wave (late systolic peak) and is related to the stiffness of the aorta. The PWV and AIx will be presented as the mean values from two recordings. The algorithm for estimation of central systolic blood pressure (cSBP) has been derived from the relationship between invasively measured cSBP and the SBP in the brachial artery, and cSBP estimated by arteriography correlates well with invasively measured cSBP [41]. Blood pressure will be measured at the same time of the day using a validated digital automatic blood pressure monitor (OMRON M6, Omron Health Care Co., Ltd., Kyoto, Japan) according to the International Protocol of the European Society of Hypertension [42].

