### Data collection and outcome measures

Outcome measures will be assessed at baseline and at 12-week follow-up by personnel blinded to the treatment allocation. Data will be recorded on standardised forms and entered into a secured-access database that contains quality control checks (e.g. range checks, notification of missing data).

The primary outcome measure is endothelial function as measured by flow-mediated dilatation (FMD). The secondary outcome variables include HR variability, pulse wave velocity (PWV), weight, BMI, WC, body composition, body temperature, biochemical profile, health-related physical fitness, self-perceived health, health-related quality of life (HRQL), and side effects. Other variables of interest include 24-hour dietary recall, lifestyle and demographic characteristics (Table 3 and Figure 3).

**Table 3 Tab3:** Summary of time point measurements of the primary and secondary outcomes of the study

Type of outcomes	Specific outcomes	Measurements		
		1-baseline (week 0)	2-moment (week 4)	3-moment (week 12)
Primary outcomes	Endothelial function as measured by flow-mediated vasodilatation	X		X
Secondary outcomes	Vascular function: heart rate variability, aortic pulse wave velocity, augmentation index and blood pressure	X		X
	Morphological component: weight, height, BMI, waist circumference	X	X	
	Body composition: fat mass and non-bone lean body mass	X		X
	Body temperature	X		X
	Plasma samples and biochemical analysis: LDL cholesterol (LDL-c), HDL cholesterol (HDL-c), total cholesterol, triglycerides, glucose, glycated haemoglobin (HbA1c)	X		X
	Fitness component: self-reported fitness, 1RM, hand-grip and peak uptake of volume of oxygen	X		X
	Self-perceived health: health-related quality of life	X		X
	Recent Physical Activity Questionnaire	X	X	X
	Demographic information	X		
	Side effects	X	X	X

*1RM* one repetition maximum, *BMI* body mass index

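### The printed augmentation index subtracts the reflected (late) peak from the early peak, so as defined it has the opposite sign to an augmentation index

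*Protocol article*

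**What the plan says.** Table 3, under Data collection and outcome measures, lists AIx among the secondary outcomes, in the row "Vascular function: heart rate variability, aortic pulse wave velocity, augmentation index and blood pressure", measured at baseline and week 12.

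The section on aortic pulse wave velocity (PWV) and AIx describes a cuff-based device whose signal passes to named software: "Both PWV and AIx will be measured with the oscillometric method using the occlusion technique". It then gives a single derivation for both versions of the index: "Both aortic AIx (AIxao) and brachial AIx (AIxbr) will be calculated as", followed by an equation. The numerator is the early systolic pressure peak minus the late systolic peak (in the equation's mark-up, "peak}-\mathrm{late}\ \mathrm{systolic}\ \mathrm{peak"), and the result is scaled by 100 over pulse pressure.

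The next paragraph fixes what the two peaks are. It defines return time as the interval between "the first (early systolic pressure peak) and reflected systolic wave (late systolic peak"). The early peak is thus the first wave and the late peak is the reflected one.

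The article gives no other AIx formula, does not describe the index as deliberately inverted, and does not say whether a rise or a fall is an improvement.

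**The concern.** An augmentation index expresses how much the reflected wave adds to systolic pressure, so its numerator should grow when the reflected peak grows. Because the article itself says that the late peak is the reflected one, the order of subtraction cannot be explained as a labelling ambiguity. The printed numerator shrinks as the late peak grows.

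What is at stake is the direction of a listed secondary vascular outcome. The trial compares exercise modes on vascular function, so which way AIx moves is the substance of that result. An analyst who derives AIx from the printed line and then reads it in the customary way (higher means more augmentation) would see less wave reflection as a higher, apparently worse, value. A reader who meets values exported with the usual sign and interprets them by the published formula would make the mirror-image mistake. Nothing in the text would alert either of them.

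**Working it through.** **Inputs.** From the PWV and AIx section: the order of subtraction, the divisor (pulse pressure), and the identification of the late peak as the reflected wave. The article gives no AIx value or pressure to reproduce, so the pressures below are assumptions for illustration. The late-minus-early convention is standard methodological knowledge and is not stated in the article.

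**Formulas.** E is the early peak, L the late peak and PP the pulse pressure.

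- Printed: AIx = 100 × (E − L)/PP
- Usual: AIx = 100 × (L − E)/PP

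Since (E − L) = −(L − E), every printed value is −1 times the usual value.

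**Effect of a 5 mmHg fall in the late peak, with E and PP held fixed.**

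| E | PP | L before → after | Printed AIx | Change | Usual AIx | Change |
|---|---|---|---|---|---|---|
| 120 | 50 | 130 → 125 | −20 → −10 | +10 | +20 → +10 | −10 |
| 120 | 50 | 110 → 105 | +20 → +30 | +10 | −20 → −30 | −10 |
| 115 | 40 | 115 → 110 | 0 → +12.5 | +12.5 | 0 → −12.5 | −12.5 |

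First row worked out: 100 × (120 − 130)/50 = −20 and 100 × (120 − 125)/50 = −10 as printed; 100 × (130 − 120)/50 = +20 and 100 × (125 − 120)/50 = +10 in the usual order.

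The reversal occurs whether the late peak lies above, at or below the early peak, so it does not depend on the pressures chosen.

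**Effect on inference.** Multiplying an outcome by −1 changes the sign of each mean and each between-arm difference and leaves every variance as it was. A t statistic changes sign and its two-sided p-value stays the same. In a simulated check with 15 values per arm, t was +3.23 for the values and −3.23 for their negatives, with p = 0.0031 both times. The planned one-way ANOVA and Kruskal-Wallis tests are equally indifferent to the sign: the F ratio depends on squares, and the ranks simply run in reverse. Only the direction of the estimate is affected.

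**The neighbouring PWV sentence.** It reads "PWV will be calculated as the jugulum and the symphysis distance (m) divided by return time (return time/2) (s"), which names return time and then half of it. With an assumed 0.50 m and 130 ms, dividing by return time gives 0.50/0.130 = 3.85 m/s, and dividing by half of it gives 0.50/0.065 = 7.69 m/s. The parenthesis already supplies the operative quantity and the sentence already gives seconds, so this is a matter of clarity and not a second error.

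**The case against.** The strongest reply is that nobody may ever compute AIx from the printed line. The cuff signal goes to the device's own software, and no step has staff recording early and late peak pressures. If that software exports the usual sign, the data are right and the article merely describes them wrongly. This stands as a limit on the consequence: the article does not say whether the software output or the printed formula supplies the analysed value. It does not rescue the formula, which is given as the rule for the outcome.

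A reader might infer something stronger: that arterial improvement will be recorded as worsening, and that AIx will appear to contradict the flow-mediated dilatation (FMD) and PWV results. The documents do not support that. Reversal requires two conventions to be mixed, with values derived one way and read the other. Someone who both derives and interprets AIx by the printed formula reaches the right direction. How AIx will line up with the other vascular outcomes is a forecast about results.

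It can also be said that no passage of the article contradicts the formula, because no favourable direction is stated, and that the error is shown by general knowledge. This is partly right: no stated figure fails to reproduce. But the name of the index, together with the article's own identification of the reflected wave, is enough to show that the order is reversed.

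**Conclusion.** The printed definition is wrong for both aortic and brachial AIx: the numerator has the opposite sign to an augmentation index, so less wave reflection gives a higher value.

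If the formula is applied as written and AIx is read on the usual scale, every non-zero AIx difference has its direction reversed. Magnitudes and two-sided p-values are unchanged. If the device software exports the usual sign, the fault is confined to the published definition. The documents do not show which case holds, so a claim that the trial's AIx results will be inverted would go too far.

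The primary outcome (FMD) and the sample size are untouched. The conclusion rests on the usual meaning of the index and on the article's own labelling of the two peaks; the illustrative pressures are assumed and only show the size of a typical sign change. The correction should be made because the formula is the stated rule for a listed secondary outcome and costs almost nothing to put right.

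**What to change.** - Print AIx = 100 × (late systolic peak − early systolic peak)/pulse pressure, for both aortic and brachial AIx.
- Confirm that the device export uses this order, and say whether the analysed values are the software's output or are derived from recorded peaks.
- State that a lower AIx is favourable.
- Optional, wording only: give the PWV denominator once, as return time/2 in seconds.

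The cost is one corrected equation, one added sentence and one check of the device output. No new data or procedures are needed.

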##### Morphological component

Anthropometric variables will be assessed by a nutritionist in accordance to the International Society for the Advancement of Kinanthropometry (ISAK) guidelines [43]. Variables will be collected at the same time in the morning, between 00.70 and 00.80 hours, following an overnight fast of at least 10–12 hours. The body weight of the subjects will be measured when the subjects are in underwear and without shoes, using electronic scales (Tanita® BC544, Tokyo, Japan). The height of the subjects will be measured using a mechanical stadiometer platform (Seca® 274, Hamburg, Germany). The BMI of the subjects will be calculated as the body weight in kilograms divided by the square of the height in metres. The WC will be measured as the narrowest point between the lower costal border and the iliac crest; in case this is not evident, it will be measured at the midpoint between the last rib and the iliac crest using a tape measure (Ohaus® 8004-MA, Parsippany, NJ, USA). The waist-to-height ratio will be computed by dividing WC by height, and this provides a surrogate measure of central body fat. We will take each measure twice and use the average measure obtained, unless the first and second measures vary by more than 1 %, in which case we will use the median of three measurements.

##### Body composition

We will also measure fat mass, lean body mass, abdominal adipose tissue and bone mineral density by conducting a dual-energy X-ray absorptiometry scan (DEXA) (Hologic, QDR 4500 W). An experienced DEXA technologist who is blinded to the study randomisation will perform the DEXA imaging studies.

##### Body temperature

We will use a thermo-infrared camera (FLIR Thermacam E60, FLIR systems, Boston, MA, USA). Images in the frontal plane will be taken from the anterior and posterior sides, according to the thermal image acquisition criteria described by Ring and Ammer [44]. During the measurement process, participants will remain in their underwear and will maintain a steady orthostatic position during the image acquisitions. The distance from the camera to the subjects will be 2.5 m. The study will be conducted according to the guidelines of the American Academy of Thermography [45]. A single investigator, trained in the use of thermographic devices, will obtain the images.

##### Plasma samples and biochemical analysis

A fasting blood sample will be obtained from the cubital vein in the early morning at the clinical care session attended by the participants in the subset. The biochemical profile will include: (1) plasma lipid triglycerides, total cholesterol, high-density lipoprotein cholesterol (HDL-c), low-density lipoprotein cholesterol (LDL-c) (by enzymatic colourimetric methods); and (2) the metabolic regulators glucose and haemoglobin A1C (HbA1c) (by enzymatic colourimetric methods). All determinations will be analysed in serum using a Cardiocheck® and A1CNow^+^® system.

##### Self-reported fitness

Self-reported fitness will be determined by the International Fitness Scale (IFIS), which is a questionnaire validated in European [46] and Colombian adults [47]. IFIS consists of a Likert-type scale (range 1–5) with five response options (very poor, poor, average, good, and very good) about perceived overall fitness; its main components include CRF, muscular strength, speed and agility, and flexibility (http://www.helenastudy.com/IFIS). IFIS has shown ‘high’ validity and ‘moderate’ to ‘good’ reliability in young adults [48]. In Colombian adults, the internal consistency and reproducibility of IFIS items was high (Cronbach’s alpha = 0.80) and the averaged ICC range was 0.90–0.96 [47].

##### Health-related physical fitness

Physical fitness will be measured using tests that have previously shown high validity and reliability levels. It will be determined using a maximum treadmill exercise test (Precor TRM 885, Treveso, Italy) following the modified Balke protocol [49], which has been extensively used [50, 51] and validated [52]. The treadmill test will use a ramp protocol where the inclination is constant (5.5 %) and the speed increased by 0.5 km/h every minute, starting at 4 km/h. Each session will begin with a 5- to 10-min warm-up at 50 W. We will ask participants to refrain from smoking for 2 hours before the test, and from drinking alcohol or doing any vigorous- or moderate-intensity activities for 48 h before the test. HRmax will be used to determine the training intensity for each participant. We will measure blood pressure prior to and during the test. Exercise will be terminated if participants are fatigued, or earlier if they fulfill the ACSM’s guidelines for ‘Indications for Terminating Exercise Testing’ [53]*.* CRF is defined as the highest recorded VO_2_ value (VO_2_max) after two of three criteria are met: (1) a plateau in VO_2_ after increase in workload, (2) a respiratory exchange ratio >1.10, and (3) a maximal HR within 10 bpm of their age-predicted maximum. Muscular fitness will be assessed using the hand-grip test (maximum hand-grip strength assessment) using a standard adjustable handle analogue hand-grip dynamometer T-18 TKK SMEDLY III® (Takei Scientific Instruments Co., Ltd, Niigata, Japan). Participants will be given a brief demonstration and verbal instructions for the test and, if necessary, the dynamometer will be adjusted according to the subject’s hand size according to predetermined protocols. Hand-grip strength will be assessed with the subject in a standing position with their shoulders adducted and neutrally rotated, and their arms parallel but not in contact with their body. The participants will be asked to squeeze the handle for a maximum of 3–5 s, but no verbal encouragement will be given during the test. Two trials will be allowed in each limb, and the average score will be recorded as peak hand-grip strength (kg). Thus, the values of hand-grip strength presented will combine the results of left- and right-handed subjects, without consideration of hand dominance. Hand-grip will be adjusted by allometric parameters defined by Jaric [54] (dynamometry/weight^0.67^). Strength in the eight exercises will be assessed at baseline and immediately after the intervention ends. A general warm-up consisting of riding a cycle ergometer for 5 min at a self-selected resistance will precede strength testing. Standardised procedures will be used to predict a one-rep max (1RM) from reps-to-fatigue barbell squats, dumbbell adductor squats, split squats, lateral adductor squat, biceps curls, dumbbell lateral shoulder raises, dumbbell military shoulder press, and dumbbell triceps curls from each participant’s performance during the preparatory training phase [55]. Progressive overload will be achieved by increasing the load when all prescribed repetitions (for a particular exercise) are achieved on two consecutive workouts [56].

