#### Blinding and randomisation methods

The randomisation into the four study arms will be performed by the Centre of Studies in Physical Activity Measurements at University of Rosario, Bogotá, Colombia, using block randomisation with a block size of four. Eligible participants will be randomly assigned after completing the baseline measurements to either the control or exercise training groups. The principal investigator will coordinate the allocation sequence, and randomisation will be computer-generated. All participants and study personnel (including investigators, trainers, and statisticians) will be blinded to treatment allocation throughout the trial protocol. Access to the allocation code will be restricted to one study statistician who will not perform the final study analyses. Randomisation will be conducted independently using sealed opaque envelopes. These procedures are also detailed in the study operations manual. Moreover, the importance of maintaining the blinding and allocation concealment will be reinforced by regularly scheduled conference calls at the sites and daily meetings with the field investigators (Fig. 1).

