#### Intervention

The participants who are randomly assigned to the intervention group will participate in the cardiometabolic programme.Usual clinical care group

This group will receive usual clinical care according to the consensus recommendations of the national goals for cardiovascular health promotion and disease reduction of the American Heart Association [31] and Colombian guidelines COLDEPORTES (in Spanish, Departamento Administrativo del Deporte, la Recreacion, la Actividad Fisica y el Aprovechamiento del Tiempo Libre) [32]. Participants will receive counselling about goals for cardiovascular health, as well as monitoring cardiovascular health over time in the Colombian population, key signs and symptoms, diet and screening for cardiometabolic risk factors. This group will be asked to maintain their level of activity during the 12-week study period.2.High-intensity interval training (HIIT) group

The HIIT protocol will be completed with fast walking or running on a treadmill with the deck inclined to reach the desired intensity. We will calculate the training energy expenditure for participants’ age ranges associated with meeting the consensus public health recommendations from the WHO [16] and the US Department of Health and Human Services [17]. Each preparatory period starts with an exercise dose of 6 kcal kg^-1^ week^-1^, which will increase progressively by 2 kcal kg^-1^ week^-1^ until week 4, where it will remain at 12 kcal kg^-1^ week^-1^ for weeks 5 to 12.

*Preparatory training phase: weeks 1–4*

To initiate our study we will use a 4-week preparatory phase of training to bring all participants up their 300-kcal goal for the session. To accomplish this they will warm up at 65 % of maximum heart rate (HRmax) (5 min); exercise for 4 × 4-min intervals at 60–80 % HRmax, interspersed with a 4-min recovery period at 55 % HRmax, at a frequency of three times per week.

*Protocol of interval training: weeks 5–12*

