**Fig. 3 Fig3:**
[figure not shown]
Schedule of enrollment, intervention and assessment*

3.Resistance training group

*Preparatory training phase: weeks 1–4*

All participants will complete a base resistance training protocol during the 2 weeks prior to the training intervention (Table 2). This phase will encompass a total of three workouts (Monday, Wednesday, and Friday) during the 4 weeks. During the adaptation phase, the subjects will expend energy up to 300 kcal at 20–50 % of one repetition maximum (1RM), for 2 × 20–30 repetitions with 1-min rest intervals. During each exercise session, participants will adhere to the 6–8 kcal kg^-1^ week^-1^ energy expenditure format. The purpose of the preparatory phase will be to instruct proper lifting technique, familiarise participants with all exercises, and ensure that the participants began the study with a comparable training base.

**Table 2 Tab2:** Resistance training programme

Programme variable	Preparatory phase	Volume	Intensity
Preparatory training phase			
Exercise prescription	20–40 % 1RM	40 % 1RM	30–50 % 1RM
Training intensity	2 × 20–30 repetitions	2 × 20–30 repetitions	2 × 20–30 repetitions
Training volume	1 min	30 s	1 min
Energy expenditure	300 kcal		
Rest time	Weeks 1 to 4		
Specific exercises			
Barbell squats			
Split squats			
Biceps curls			
Dumbbell lateral raises shoulder			
Dumbbell military shoulder press			
Dumbbell triceps curls			
Resistance training protocol			
Exercise prescription	40–60 % 1RM	70 % 1RM	70–80 % 1RM
Training intensity	4 × 20–30 repetitions	4 × 20–30 repetitions	4 × 20–30 repetitions
Training volume	1 min	30 s	1 min
Energy expenditure	500 kcal		
Rest time	Weeks 1 to 4		
Specific exercises			
Barbell squats			
Dumbbell squats adductor			
Split squats			
Lateral adductor squat			
Biceps curls			
Dumbbell lateral raises shoulder			
Dumbbell military shoulder press			
Dumbbell triceps curls			

Volume = sets × repetitions. *1RM* one repetition maximum

*RT protocol: weeks 5–12*

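### The only 1RM method described draws on the preparatory training phase, which conflicts with the week-0 baseline scheduled for 1RM and with the arm descriptions

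*Protocol article*

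**What the plan says.** The statements that bear on baseline 1RM are spread over several sections of the protocol article.

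- **Health-related physical fitness, timing:** "Strength in the eight exercises will be assessed at baseline and immediately after the intervention ends".
- **Table 3 (Data collection and outcome measures):** the row "Fitness component: self-reported fitness, 1RM, hand-grip and peak uptake of volume of oxygen" is marked at week 0 and week 12, not at week 4, and is not restricted to particular arms.
- **Health-related physical fitness, method:** 1RM is predicted from repetitions to fatigue in eight named exercises, "from each participant’s performance during the preparatory training phase". No other 1RM method is given.
- **Blinding and randomisation methods:** "Eligible participants will be randomly assigned after completing the baseline measurements".
- **Intervention, HIIT group:** the preparatory phase is weeks 1–4 on a treadmill: "exercise for 4 × 4-min intervals at 60–80 % HRmax, interspersed with a 4-min recovery period at 55 % HRmax".
- **Intervention, usual clinical care group:** no preparatory phase is described. "This group will be asked to maintain their level of activity during the 12-week study period".
- **Intervention, resistance training group:** the preparatory phase is headed weeks 1–4, with resistance workouts on three days a week in which subjects "expend energy up to 300 kcal at 20–50 % of one repetition maximum (1RM"). The combined group receives this protocol together with HIIT.
- **Same subsection, opening sentence:** every participant is said to complete a base resistance programme in the two weeks preceding the training intervention.

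**The concern.** A baseline used to measure change, or as a covariate, has to be taken before treatment can affect it and in the same way in every arm. The article schedules such a value for 1RM, but the method it describes draws on a phase that, on its own labels, is the first third of the allocated programme and is resistance work in only two arms.

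The Statistical analyses section treats each outcome as a pair of measurements, at baseline and at 12 weeks, and plans a longitudinal model that accounts for baseline differences. The source of the baseline therefore matters. Resistance training is one of the two factors in the 2 × 2 design, and 1RM is a listed outcome that it targets directly. If site staff follow the method sentence, early gain in the resistance and combined arms is counted as baseline, while the HIIT and usual-care arms have no value from that source.

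**Working it through.** There is no stated figure to reproduce. The check is a comparison of timing and coverage, with two counts.

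**1. Timing.** Baseline measurements come first, then randomisation (Blinding and randomisation methods), then the preparatory phase in weeks 1–4 (Intervention). A value obtained during weeks 1–4 is therefore post-randomisation and cannot be the week-0 value of Table 3.

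**2. Arms.** Resistance work in the preparatory phase, from the arm descriptions:

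| Arm | Preparatory phase, weeks 1–4 | Source for the described 1RM prediction |
|---|---|---|
| Usual care | none described | no |
| HIIT | treadmill intervals | no |
| RT | resistance workouts | yes |
| Combined | RT protocol plus HIIT | yes |

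With 15 planned per arm, 2 × 15 = 30 of 4 × 15 = 60 participants (50 %) have no preparatory resistance performance.

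**3. Exercises.** Table 2 lists eight exercises in the main protocol and six in the preparatory phase. The two missing are the dumbbell adductor squat and the lateral adductor squat. So 8 − 6 = 2 of the 8 tested exercises have no preparatory data even in the RT and combined arms.

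**4. Order of dependence.** Preparatory loads are expressed as a percentage of 1RM. If 1RM is known only from performance in that phase, the loads refer to a quantity not yet available. This disappears if a week-0 1RM exists.

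**5. Effect on the estimate.** Let G be the true gain from week 0 to week 12 in an arm doing resistance work, and g the part already achieved when the preparatory prediction is made. Change measured from that prediction is G − g, so g is lost in those arms only. If the week-0 test is the baseline, g = 0 and nothing is lost. The document gives no data on g.

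**6. The conflicting sentence.** Taken literally, the opening sentence of the resistance subsection puts resistance work in all arms before training starts. If that also preceded randomisation, six of the eight exercises could have a fair common baseline. But the sentence stands under the RT heading, beside a weeks 1–4 label and a statement that the phase runs over four weeks. It also does not match the treadmill-only HIIT preparation or the absence of any training in the usual-care description. It leaves the same two exercises uncovered.

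**The case against.** The strongest reply is that the method sentence never calls its 1RM the baseline value. Just before it, the article promises a baseline strength assessment and a warm-up ahead of strength testing. Table 3 schedules 1RM at week 0 for everyone, and the next sentence concerns progressive overload. On that reading the preparatory-phase prediction only sets training loads. It also cannot produce the post-intervention value, so it cannot be the whole outcome method.

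Much of this stands, and the load-setting reading is possible. Against it, the sentence sits in an outcome section, directly after the testing sentences, and names eight exercises, matching the strength test and not the six-exercise preparatory programme. The text does not settle which reading is meant. The point is this conflict, not that a condensed article omits testing detail.

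A reader might go further and infer that 1RM has no valid baseline, or that no randomised comparison of strength is possible. The document does not support either. A week-0 assessment is scheduled without arm restriction. Even without it, a between-arm comparison of week-12 1RM would still be randomised. Hand-grip strength has its own method and its own week-0 and week-12 schedule.

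**Conclusion.** The concern holds as an internal contradiction. The one 1RM method described does not fit the scheduled week-0 baseline, the order of randomisation or the arm descriptions. If it is used as the baseline, change in 1RM is treatment-affected in the RT and combined arms and unavailable for the 30 participants planned in the other two, with 2 of 8 exercises uncovered throughout. The count of 30 rests on the arm descriptions and would change if the sentence about all participants were the correct one.

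The size of any bias cannot be derived. A reader might assume a linear 12-week gain and infer that a baseline read at the end of week 2 or week 4 hides 2/12 = 17 % or 4/12 = 33 % of it. The article gives no gain curve, and the figure is 0 % if the week-0 test is the baseline. These percentages are illustrations, not findings.

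The consequence is confined to 1RM, one item in a secondary-outcome row. The primary outcome, flow-mediated dilatation, is untouched. It should be corrected, but it does not threaten the trial's main conclusion.

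**What to change.** In Health-related physical fitness:

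- State that the outcome 1RM for all eight exercises is predicted from a repetitions-to-fatigue test at the scheduled week-0 visit, before randomisation, and again at week 12, in all four arms.
- State that week-12 1RM is analysed with adjustment for the week-0 value.
- State whether the prediction from the preparatory phase serves load-setting only.

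Across Intervention, Table 2 and Health-related physical fitness, reconcile who does the preparatory resistance phase, when it takes place relative to randomisation and week 1, and which 1RM its loads refer to. Which training rule applies is for the investigators to decide; the statements need to agree.

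The cost is small. If week-0 testing in every arm is already intended, as Table 3 indicates, only wording changes. If it is not, the HIIT and usual-care arms need the test added. A minor downside is that predictions from untrained lifters are somewhat noisier.
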